| **2.1**  **Research question/objective(s) of the study** | The aim is to assess the association between antibiotic use and risk of subsequent urinary tract infections in adults.  ***Background***  Urinary tract infections (UTIs) encompass a spectrum of infectious syndromes that affect the urinary tract anywhere from the urethra to the kidneys and are one of the most common infections, particularly in primary care (Al Hawati, Blair & Larnard). In 2023, the UTI incidence in primary care was 20 cases per 1.000 registered men and 117 cases per 1.000 registered women (Nivel, 2024). Not only is the UTI incidence higher in women than men, it also increases with age (Ahmet et al., 2018).  Women are particularly susceptible due to the close proximity of the rectum to the urethra as well as a relatively short urethral length (Li & Leslie, 2023). It is reported that 50-60% of women have at least one UTI in their lifetime (Al Hawati, Blair & Larnard, 2023). Most UTI are caused by bacteria from the gut  (Worby et al. 2022).  Most patients with UTIs can be treated relatively simple with oral antibiotics, although treatment failure occurs. Around 20-30% of women with an initial UTI will experience a recurrent UTI within 3-4 months of initial infection (Foxman, 2003). Furthermore, some UTIs can become complicated through a pyelonephritis, prostatitis, and urosepsis, which are associated with morbidity and mortality (Sabih & Leslie, 2023).  A healthy vaginal microbiota is low-diverse and dominated by *Lactobacillus crispatus*.  Vaginal lactobacilli have been touted to prevent invasion of uropathogens, for instance by creating an acidic environment. Disruption of the vaginal ecosystem, causing an overgrowth of anaerobic bacteria or yeasts, increases the risk of vaginal infections such as sexually transmitted infections (Stapleton, 2016, Herthelius 1988). Conversely, treatment that restores a Lactobacillus-dominated microbiota is associated with lower risk of recurrent UTIs. Usage of antibiotics can alter the microbial community (Chee, Chew & Than, 2020).  In pre-menopausal women, factors related to sexual behaviour are major risk factors for UTIs. These include: having a new sexual partner, increased frequency of sexual intercourse as well as the use of spermicide-containing contraceptives (Hooton, 2001). Sexual behaviour is less firmly associated with UTIs in post-menopausal women, where age-, hormonal- and disease-related urogynaecology and immune factors play a more prominent role. An increased postvoid residual urine volume, the presence of bladder prolapse and urinary incontinence have been associated with UTIs (Athanasiou et al., 2010). Antibiotic use or treatment of asymptomatic bacteriuria has also been associated with the development of UTIs (Cai et al., 2014, Smith et al. 1997).  To date, only one small-scale study has been conducted on this subject, which indicated a potential correlation between antibiotic use and an elevated risk of urinary tract infections in pre-menopausal women (Smith et al. 1997). To our knowledge, there are no studies whether this also holds for postmenopausal women and men.  In this study, we would like to evaluate whether different antibiotics (either to treat UTI or other infections) are associated with increased risk of UTI in premenopausal women, postmenopausal women and men. If this association can be confirmed, the next would be to study effective preventive measure for an UTI. This would be highly beneficial, as urinary tract infections represent a significant burden for patients, while antibiotic use is also the major contributing factor to the development of antibiotic resistance. |

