| --- | --- |

1. **Study design**

| **3.1**  **a. General description of the study design** | This research project will use the data infrastructure Extramural Leiden Academic Network (ELAN).  ELAN provides access to and the use of pseudonymized healthcare data from various cooperating partners such as healthcare data of general practitioners. The study period concedes 2014-2024.  ***Question***  Is antibiotic use associated with increased risk for urinary tract infection in adults?  Further explorations will be done to what extent the increased UTI risk of antibiotic use holds for:   - Different antibiotics or antibiotic classes - Men versus women - Post- versus Premenopausal women - Indication for antibiotic treatment (excluding UTI’s)   A self-controlled cases series (SCCS) design will be employed to establish the risk for developing an UTI within 3 months after antibiotic treatment compared to patients with an UTI who did not receive an antibiotic treatment. With the SCCS design, patients will be their own control.  The primary endpoint is risk of a UTI within 3 months after initiation of antibiotic treatment computed as an odds ratio.  An antibiotic treatment is defined as the exposure. An UTI between 2 weeks and 3 months after antibiotic treatment is defined as an event. The first 2 weeks after start of the treatment, patients are still somewhat protected by the antibiotic use against a new infection. And if a new antibiotic treatment is needed within 2 weeks after start of treatment, this is considered as treatment failure of the initial treatment.  Descriptive analysis will be performed for exposures, outcomes and covariables for the whole population of analysis and stratified by antibiotic use or not.  Multivariable logistic regression analysis will be performed to assess whether there is an association of antibiotic use with developing a UTI within 3 months after initiation of treatment. First a crude model will be used followed by confounder adjusted models. Confounders are season variability (Winter, spring, summer and autumn) and risk factors for UTI and selected based on theory or literature (Tj VanderWeele 2019). Risk factors are a history of an UTI, urine incontinence, urolithiasis, pregnancy, urine catheter, anatomical / functional abnormality urinary tract, immunocompromising comorbidities such as HIV/AIDS ,Type 2 Diabetes Mellitus.  **Subgroup analysis**  Subsequently, subgroup analysis will be performed to examine whether the association differs upon specific type of antibiotic treatment. For each subgroup, we will calculate an odds ratio for an UTI after antibiotic treatment. Subgroups are antibiotic(group)s, gender and age, type of infection and social determinants .  *Most used antibiotic(group)s in primary care*:   - Amoxicillin - Amoxicillin/clavulanic acid - Flucloxacillin - Tetracyclines - Macrolides - Fluoroquinolones - Trimethoprim - Co-trimoxazole - Fosfomycin - Nitrofurantoin   *Type of infection*   - All infections - UTI - non-UTI (all other infections)   *Gender and age*   - Men - Premenopausal women, defined as < 50 years of age - Postmenopausal women, defined as ≥ 50 years of age   *Social determinants*   - Socio-economic status (SES) - Migrant background |

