| **4.7**  **Is the use of (medical) data for scientific purposes recorded in the medical record of the relevant patient(s)?** | No explicit note is made per patient in the EPD of the general practitioner, because most general practitioner systems are not (yet) designed for this. It is, however, recorded which patients object to reuse their data for research and it is not used for research. |
| **4.8**  **a. By whom will the required data be extracted from the patient records?**  **b. Are the individuals who extract the required data from the patient records authorized to do so on the basis of a treatment relationship with the respective patients?**  **c. If the answer to question 4.8 is no: are the individuals who extract the data from the patient records under the direct supervision of a clinician who, by virtue of a treatment agreement, is authorized to access the records? If so, please state the name and position of the relevant clinician(s).** | The data is extracted from the file by an external party, as described in the governance document of the ELAN data warehouse: <https://www.lumc.nl/sub/4070/att/1914340/ELAN-Gov-okt2019>.  The external party is the Foundation for Information Provision for Care and Research (STIZON), which has entered into a service and processing agreement for this with the general practitioner. STIZON is ISO 27001 and NEN 7510 certified.  No.  Yes, the general practitioners (patients' caregivers) have instructed STIZON (see above) to extract and provide pseudonymized patient data from the general practitioner information system for the ELAN data warehouse. Processor agreements and / or service agreements have been signed for this between GPs and the data supplier. |
| **4.9**  **Will personally identifiable data be made available to the researcher(s)?** | No, conversion to individual natural persons is reasonably prevented. Analyzes are performed in the secure setting of CBS. Before the results can be exported from the CBS environment, the CBS carries out a mandatory output check where the risk of disclosure is checked. Every result from this research must comply with the output guidelines of the CBS (see Appendix B). For example, all tables and similar output must contain at least 10 units (unweighted) as the basis for each cell or data point. In this way it is independently tested and guaranteed that no data traceable to an individual or institution can be used. |

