| **6.1**  **a. Primary outcome**  **b. Secondary outcome** | ***Primary outcome***  What is the association of antibiotic use for any infection with risk for urinary tract infection in adults?   - Odds ratio for an UTI after antibiotic use in the preceding 3 months   - Per infection group, antibiotic for     - All infections     - An UTI     - An infection expect UTI’s   - Per antibiotic (group)   - Per patient group     - Men     - Women < 50 years of age     - Women ≥ 50 years of age   - Social determinants     - SES     - Migrant background   - Combinations of each subgroup   ***Secondary outcome***   - Hazard ratio for an UTI after antibiotic use in the preceding 3 months   - Per infection group, antibiotic for     - All infections     - UTI     - non-UTI   - Per antibiotic group   - Per patient group     - Men     - Women < 50 years of age     - Women ≥ 50 years of age   - Social determinants     - SES     - Migrant background   - Combination of each subgroup - Incidence of an UTI per month |
| --- | --- |
| **6.2**  **a. Statistical analysis primary outcome**    **b. Statistical analysis secondary outcome** | ***Primary outcome***  The Odds ratio for an UTI after antibiotic treatment the preceding 3 months will be calculated through a logistic regression model.  Risk factors and season variability are defined as confounders in this logistic regression model. Risk factors are a history of an UTI, urine incontinence, urolithiasis, pregnancy, urine catheter, anatomical / functional abnormality urinary tract and Type 2 Diabetes Mellitus. An Odds ratio for an UTI will be attributed to each confounder based on a critical literature appraisal.  ***Secondary outcome***  Cox proportional hazard regression models will be used to examine the associations between an UTI after antibiotic treatment the preceding 3 months.  Survival time (in days) was defined as the period between 14 days after the start of the antibiotic treatment and an UTI. The hazard ratio will be adjusted with the previous described confounders (see primary outcome).  The incidence of each UTI will be calculated for each month during 10 years to examine the season variability. |

1. **Appendices and references**

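### Subgroup odds ratios are meant to show whether the association differs, but no between-group contrast is fixed, and section 6.1 lists every subgroup and combination as primary although 3.1 calls most of them exploratory

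*Protocol*

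**What the plan says.** **Status of the subgroups.** Protocol section 3.1 defines one primary endpoint: "The primary endpoint is risk of a UTI within 3 months after initiation of antibiotic treatment computed as an odds ratio". It introduces antibiotic class, men versus women, post- versus premenopausal women, and indication with the words "Further explorations will be done to what extent the increased UTI risk of antibiotic use holds for". Section 6.1 opens the primary outcome with the overall question (antibiotics for any infection, all adults). Under that same heading it lists odds ratios per infection group, antibiotic, patient group, SES and migrant background, and finally "Combinations of each subgroup". The same grid is repeated for hazard ratios under the secondary outcome.

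**Aim of the subgroups.** Section 3.1 states that "subgroup analysis will be performed to examine whether the association differs upon specific type of antibiotic treatment", and then widens the scope: "Subgroups are antibiotic(group)s, gender and age, type of infection and social determinants".

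**Method for the subgroups.** Section 3.1 gives one: "For each subgroup, we will calculate an odds ratio for an UTI after antibiotic treatment". Section 6.2 adds a confounder-adjusted logistic model (primary) and a Cox model (secondary). Neither section names a term or contrast that compares one subgroup with another.

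**The concern.** There are two linked problems, and both lie in what the protocol states.

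First, the method does not answer the question. Whether an association differs between two groups is a statement about the ratio of their odds ratios and its uncertainty. Two odds ratios set side by side invite the comparison of one that excludes 1 with one that does not. That comparison can show a contrast where none exists, or hide one that does, particularly when the groups contribute very different numbers of events. Section 2.1 makes this likely for sex: "In 2023, the UTI incidence in primary care was 20 cases per 1.000 registered men and 117 cases per 1.000 registered women".

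Second, sections 3.1 and 6.1 give the same analyses different standing. A report that follows 6.1 literally could present any one of dozens of cells as a primary result, although 3.1 would class most of the underlying questions as exploratory.

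**Working it through.** The protocol states no significance level, power or sample size, so it has no figure of its own to reproduce. The calculations below assume two-sided 5% per odds ratio.

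**1. Counting the odds ratios (sections 3.1 and 6.1)**

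- Levels listed: 10 antibiotic groups, 3 infection types, 3 patient groups. The all-infections level is the union of the other two, so 2 infection types are distinct.
- SES and migrant background have no stated levels. I assume 2 + 2 at the low end and 5 + 3 at the high end.
- Single-factor subgroups: 10 + 3 + 3 = 16 without social determinants; 16 + 4 = 20 or 16 + 8 = 24 with them.
- Combinations before social determinants: 10 × 2 × 3 = 60 distinct, or 10 × 3 × 3 = 90 as listed.

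**2. Chance of at least one false positive**

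With all nulls true and independent tests, the chance is 1 − 0.95^m and the expected number is 0.05 × m.

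| m | Chance of at least one | Expected number |
|---|---|---|
| 16 | 56.0% | 0.8 |
| 20 | 64.2% | 1.0 |
| 24 | 70.8% | 1.2 |
| 60 | 95.4% | 3.0 |
| 90 | 99.0% | 4.5 |

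The subgroups overlap, so independence is an upper reference. Simulation with equally correlated test statistics gives:

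| m | rho 0.3 | rho 0.5 | rho 0.7 |
|---|---|---|---|
| 20 | 54% | 42% | 29% |
| 60 | 84% | 67% | 43% |
| 90 | 93% | 75% | 48% |

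**3. Significant in women only, when the true effects are equal**

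Inputs: the incidence ratio from section 2.1 is 117/20 = 5.85. I assume groups of equal size and information proportional to events. If the test statistic in women has mean d, in men it has mean d/√5.85 = d/2.42. The probability is power(women) × (1 − power(men)).

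- Women at 90% power: d = 1.96 + 1.28 = 3.24. In men, 3.24/2.42 = 1.34, so power = Φ(1.34 − 1.96) = 0.27. Result: 0.90 × 0.73 = 66%.
- One age group of women against men, women's events split evenly (assumed): the ratio is 5.85/2 = 2.9, and 3.24/√2.925 = 1.89. Power in men = Φ(1.89 − 1.96) = 0.47. Result: 0.90 × 0.53, about 47%.
- Men at 90% power: power in women is practically 1. Result: 1 − 0.90, about 10%.
- Men at 99% power: about 1%.

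A direct test of the ratio of odds ratios at 5% would declare a false difference 5% of the time, whatever the power in either group.

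**4. Many subgroups of one factor**

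For k independent subgroups with the same true effect and the same power p, the chance that they disagree on significance is 1 − p^k − (1 − p)^k. For the ten antibiotic groups this is 89% at p = 0.8, 65% at p = 0.9 and 10% at p = 0.99. For two groups it is 32%, 18% and 2%.

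**The case against.** The strongest reply has several parts.

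- *The primary contrast exists.* A reader might infer from 6.1 that there is no single primary contrast. The text does not support that. Section 3.1 names one endpoint, and 6.1 begins with any antibiotic in all adults; the subgroups hang beneath it. What remains is a conflict over the standing of the subgroups.
- *The protocol never says it will compare p-values.* This is correct. It states no threshold, and asking to what extent an association holds can be read as estimation. For disjoint groups such as men and women, a reader could form the ratio of odds ratios from separate estimates and confidence intervals. But 3.1 sets out to examine whether the association differs, and the plan does not itself provide that contrast. For antibiotic groups, the same patients may contribute to several estimates, so the ratio cannot simply be formed from independent results.
- *Multiplicity rules and significance levels belong in an SAP.* I accept this, and their absence is not held against the protocol. The point rests on the method and labels that the protocol does fix.
- *Chance findings and false differences are not near certain.* A reader might infer that they are. For chance findings this fits only the full grid of combinations, read at 5% with nearly independent tests. For false differences it does not hold in general: ten years of data from a GP network may give very high power in the main groups, and the probability is then small. The 66% is one scenario among several. It also takes women as a single group, whereas 6.1 splits them at age 50.
- *The disclosure rule.* Section 4.9 requires that "all tables and similar output must contain at least 10 units (unweighted) as the basis for each cell or data point". A reader might infer selective reporting of sparse combinations. This is an external disclosure control, not an analysis choice, and I draw no conclusion from it.

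**Conclusion.** The point holds in two parts, neither of which depends on the calculations: the fixed method does not address the stated question of difference, and 3.1 and 6.1 conflict on whether the subgroups are exploratory or primary.

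The size of the consequence is conditional. At an assumed 5% per odds ratio, with all nulls true and independence, at least one false positive has a probability of about 56% to 71% over the single-factor subgroups and 95% to 99% over the combinations. Correlation lowers these figures, to 48% for 90 combinations at rho 0.7. An apparent difference between women and men with equal true effects has a probability of about 10% to 66% over the power assumptions examined, and less at very high power. The protocol gives no sample size from which to narrow that range.

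The change is worth making before the analysis. It does not call the overall odds ratio into question.

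**What to change.** 1. In section 6.1, keep the overall odds ratio (any antibiotic, all adults) as the only primary result. Move all subgroups to secondary or exploratory, in agreement with 3.1.
2. For sex/menopausal group, SES and migrant background, fit exposure-by-modifier interaction terms in one model. Report the ratio of odds ratios with a 95% CI, next to the group-specific estimates.
3. For antibiotic group and indication (UTI versus non-UTI), use a multi-level exposure variable and report contrasts between its levels with 95% CIs. These are attributes of the exposure and are undefined when a patient is unexposed, so an interaction term cannot be used.
4. Delete the line on combinations of subgroups, or limit it to antibiotic group by patient group, labelled exploratory. Treat the hazard-ratio grid in the same way.

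The cost is wording and additional model terms; no new data are needed. Fewer results will carry the primary label, and the contrasts will be less precise than the single-group estimates: for two independent groups the standard error of the log ratio is √(SE₁² + SE₂²), or 1.41 times a single SE when the two are equal. That imprecision is the true uncertainty about a difference.

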| --- | --- |
| **3.2**  **a. When will the study be conducted?**  **b. What is the intended end date of the study?** | The research will be performed as part of a MSc. Internship ([name]) in the period between February 2025 and June 2025.  Month 1 – Literature research, writing the introduction, first part of data preparation.  Month 2 – Writing the introduction and methodology, second part of data preparation.  Month 3 – Completing the introduction, methodology and data preparation, start of data analysis.  Month 4 – Completing the data analysis and writing the results.  Month 5 – Writing the report, focusing on the discussion.  The end date is July 2025. |
| **3.3**  **Does the study involve exclusively existing (patient) data (retrospective) and not data yet to be generated (prospective)?** | This study includes already existing data only, and is thus retrospective (see also 3.1). |
| **3.4**  **What type of data will be used for the research?** | Pseudonymized routine care patient data from GP practices participating in ELAN. |
| **3.5**  **If information from patient records is used: describe what type of information is involved.** | The dataset from ELAN contains data over a period of 10 years and includes:   - Number of all included patients in ELAN per year - All patients with an UTI   - ICPC code U70, U71, including subcodes   - Date of registration with GP office - Antibiotic prescriptions ATC J01 for all patients with an UTI   - Corresponding medical diagnosis with the antibiotic prescription by ICPC code   - Details on the antibiotic prescription (name of antibiotic, dose and duration) - Characteristics of included patients   - Year of birth   - Year of death   - Sex   - Referral to urologist for recurrent UTIs   - Risk factors for an UTI     - History of UTI ICPC code U70, U71     - Urine incontinence ICPC code U04     - Urolithiasis ICPC code U95     - Urine catheter ICPC code U28     - Anatomical / functional abnormality urinary tract ICPC code U85     - Type 2 Diabetes Mellitus ICPC code T90.02     - Prostate hypertrophy ICPC codes Y06, Y85     - Medication use for miction problems with ATC codes     - G04BD     - G04C     - Social economic status     - Migrant background |
| **3.6**  **To which time period do the data relate?** | The period between 2014 and 2024 |

1. **Data storage and privacy**

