| **4.1**  **a. In the context of this study, will patients/participants be asked for consent to use their (medical) data?**  **b. If no consent is requested: please explain why consent will not be sought.** | In general, it can be stated for the ELAN data warehouse that, in accordance with current guidelines, patients are given the opportunity, through an informed opt-out procedure, to NOT make their pseudonymized and coded data available for scientific research. To inform patients, (digital) posters are hung in the waiting rooms. There are also leaflets available that patients can take with them. The information also appears on the websites of the practices (see supplement A).  Not applicable |
| --- | --- |
| **4.2**  **Have patients/participants previously been asked for consent to use their (medical) data for scientific research?** | See 4.1 |
| **4.3**  **a. Is there (or has there been) a treatment relationship between the researcher(s), or the researcher(s)’ department, and the patients whose records are being reviewed? (see also section 4.8 below)**  **b. Is the treatment relationship still ongoing, or has it since been terminated?** | Yes, two of the researchers ([name], [name]) worked as a general practitioner in the region where the research is done. Next to pseudonymization of patients, details on GP and GP practice is pseudonymized as well.  The principle investigator of this project has stopped working in one of the ELAN data warehouse practices and there is no longer a treatment relation. |
| **4.4**  **Is it likely that patients from the study population have since passed away?** | Yes, this is a possibility. |
| **4.5**  **For how many patients will data be used?** | The study will use data of all patients of 18 year and older in the ELAN data warehouse. |
| **4.6**  **Have patients had the (general) opportunity to object to the (coded/anonymized) use of their (medical) data?** | Yes, within the framework of the ELAN data warehouse, registered patients are informed by participating GPs about the reuse of their medical data for scientific research, with leaflets and posters. Hereby they are offered the opportunity to lodge an objection (informed opt-out procedure). |

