| **4.10**  **If coding takes place: when will coding occur, by whom, and in what manner?** | Coding is done by STIZON and CBS |
| **4.11**  **Has a notification of the intended data processing been submitted via:**  <https://www.albinusnet.nl/weten-en-regelen/juridische-zaken/privacy/meldenverzamelenonderzoeksdata/>**?** | Yes |
| **4.12**  **If applicable: where will the coded data be stored, and who will have access to the coded data?**  **If applicable: where will the uncoded data be stored, and who will have access to the uncoded data?** | The coded data is stored, and a specific research folder assigned to the department disk (I: \) of PHEG. Only the researchers involved ([name] and [name]) and the PHEG data manager have access to this folder.  There is no storage of uncoded data. |
| **4.13**  **What technical and organizational measures have been taken to prevent loss, theft, or unauthorized use of the research data? For example, is a data safe being used?** | The data never physically leaves the research folder of the LUMC or the remote access CBS environment and see 4.12. |
| **4.14**  **By whom is the code key managed?** | STIZON. |
| **4.15**  **Will (research) data be shared with another institution(s) within the Netherlands and/or the EU?** | No. |
| **4.16**  **a. Will (research) data be shared with another institution/organization outside the EU?**  **b. Will the relevant patients be asked for consent to share their personal data with a country outside the EU?** | No.  Not applicable. |
| **4.17**  **How long will the (research) data be retained? If the data will be kept for longer or shorter than the standard retention period of 15 years, please explain why.** | After processing, the research data is returned to ELAN in accordance with the data transfer agreement. The LUMC department PHEG will keep the research data for 15 years. |

1. **Research population**

| **5.1**  **Inclusion criteria** | Adults patients 18 year and older with an acute UTI and registered at an GP office for a least 1 year |
| --- | --- |
| **5.2**  **Exclusion criteria** | Patients younger than 18 years of age.  Patients with antibiotic prophylaxes  UTIs are excluded as an event if   - During pregnancy - within 3 months after giving birth - within 1 year prior to an UTI (wash-our period) |

1. **Statistical analysis**

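### History of UTI is adjusted for in a sample selected on having a UTI, where it gives little or no control of UTI-proneness; the model should condition on the person

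*Protocol*

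**What the plan says.** Who is in the data:

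- Protocol 3.5 lists cases by "ICPC code U70, U71, including subcodes" and exposure as "Antibiotic prescriptions ATC J01 for all patients with an UTI". For everyone else it lists only "Number of all included patients in ELAN per year".
- Protocol 5.1 includes "Adults patients 18 year and older with an acute UTI and registered at an GP office for a least 1 year".
- Protocol 4.5 contradicts both: "The study will use data of all patients of 18 year and older in the ELAN data warehouse".

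What is adjusted for:

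- Protocol 6.2: "Risk factors are a history of an UTI, urine incontinence, urolithiasis, pregnancy, urine catheter", followed by further conditions. Section 3.1 gives a similar list, also starting with history of UTI. Section 6.2 carries the list into the Cox model.
- Protocol 3.5 defines that first item as "History of UTI ICPC code U70, U71", without an index date or look-back period. The data cover 2014-2024, and no earlier records are listed.

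Which model: section 3.1 names a self-controlled case series in which each patient is his or her own control. It then compares treated patients with UTI patients who had no antibiotic, using multivariable logistic regression. Section 6.2 repeats the logistic model and does not mention conditioning on the patient.

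**The concern.** UTI-proneness differs between patients, and it is the obvious between-patient confounder of antibiotic use and later UTI. History of UTI is the covariate meant to capture it.

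Everyone in the extract has at least one UTI. A patient observed at a time with no earlier UTI must still have one later in the window, or would not be in the data. A patient who has already had one need not have another. Selection therefore creates an inverse association between earlier and later UTI that works against the true positive one. A covariate whose association with the outcome has been cancelled in this way cannot remove confounding, yet the result would still be reported as confounder-adjusted.

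This follows from the sampling rule and the covariate definition, both of which the protocol fixes. A self-controlled analysis would not have the problem. The between-person logistic model written under that label does.

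**Working it through.** The protocol states no figure to reproduce, so the check is on the mechanism and its size.

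**Inputs.** From Protocol 2.1: 117 UTIs per 1,000 women and 20 per 1,000 men per year, i.e. 0.117 and 0.020. From 3.5: a 10-year window, treated here as 40 quarters, with a quarter standing in for the 3-month risk period. Assumed: the spread of UTI-proneness (gamma frailty, variance 0 to 4); non-UTI antibiotic use of 8% per quarter, proportional to frailty to the power 0.5; a true antibiotic odds ratio of 1.

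**Step 1: selection alone, by hand.** Give every woman the same risk, so that the true history odds ratio is 1.

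- Quarterly odds: 0.117/4 = 0.02925. Risk p = 0.02925/1.02925 = 0.02842.
- No UTI in 40 quarters: (1 - p)^40 = 0.3156, so 0.6844 enter the extract.
- Mean quarter of first UTI among those who enter: 1/p - 40 × 0.3156/0.6844 = 35.19 - 18.45 = 16.74.
- Each such patient has exactly one event in 16.74 history-free quarters: odds 1/15.74 = 0.0635.
- After the first UTI the odds are again 0.02925.
- History odds ratio in the extract: 0.02925/0.0635 = 0.46.

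Simulation of the same case gives 0.46 in UTI patients and 0.99 in all adults.

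**Step 2: with differing proneness.** Pooled logistic regression on person-quarters, 60,000 simulated people, history = any earlier UTI in the window:

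| UTI rate/yr | Frailty variance | History OR, all adults | History OR, UTI only | Antibiotic OR, UTI only: crude → adjusted |
|---|---|---|---|---|
| 0.117 | 1 | 2.22 | 0.66 | 1.19 → 1.21 |
| 0.117 | 2 | 3.59 | 0.80 | 1.34 → 1.35 |
| 0.117 | 4 | 7.10 | 1.03 | 1.58 → 1.58 |
| 0.020 | 2 | 3.17 | 0.24 | 1.11 → 1.13 |

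Other frailty and exposure settings extend the history odds ratio to about 1.15 in UTI patients and 8.9 in all adults. Adjustment removes essentially nothing in UTI patients. In all adults it removes part (2.25 to 1.75 at 0.117, variance 2).

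**Step 3: the same UTI patients, analysed within person.** For non-UTI antibiotics the within-person Mantel-Haenszel odds ratio was 0.96-1.02 in every run with a true value of 1, and 1.50 when the truth was 1.5.

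**Step 4: sensitivity to what the protocol leaves open.**

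- No link between proneness and antibiotic use: 1.02 crude, 1.03 adjusted, so no inflation to remove.
- Steeper link (use proportional to frailty; 0.117, variance 2): 1.78 crude, 1.82 adjusted.
- 12-month look-back: history odds ratio 0.43-1.59; largest change in the antibiotic odds ratio 1.55 to 1.49.
- History from the 10 years before the study: 1.18-2.49, with partial adjustment (1.56 to 1.41 at best), but 3.5 lists no such data.
- Event dependence (a UTI raises the risk of the next by an assumed factor of 2-5) with a 12-month look-back: history odds ratio 2.1-2.6; antibiotic odds ratio 1.35 to 1.28 and 1.26 to 1.21.
- UTI-indicated antibiotics counted as exposure, truth 1: the within-person estimate is itself biased, about 0.80-0.88, or 1.14-1.97 with event dependence.

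The runs are logistic. For the Cox model the point rests on the same sampling argument and was not simulated separately.

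**The case against.** Five counter-arguments deserve weight.

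**The look-back is open.** It may be settled in an analysis plan not at hand, and Protocol 2.1 reports 20-30% recurrence within 3-4 months, while runs with frailty alone gave 4-7% in the quarter after a first UTI. With event dependence and a short look-back the coefficient has the right sign and the adjustment helps. This stands. A reader might infer that the adjustment can never do anything, or that the coefficient must be null or reversed; the protocol does not fix the definition tightly enough for that. A 12-month look-back would, however, coincide with the one-year wash-out in 5.2. That wording is unclear, but if it removes events with a UTI in the preceding year, 12-month history is zero for every event.

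**Inflation is assumed.** This also stands. A reader might infer that the antibiotic odds ratio is bound to be inflated. No figure in the protocol shows that UTI-prone patients receive more antibiotics for other infections, and selection on UTI itself shrinks the bias compared with all adults.

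**The protocol names a self-controlled design, for which a case-only sample is valid.** True, and that points to the remedy. It does not rescue the between-person logistic model actually specified.

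**Section 6.2 takes confounder odds ratios from the literature.** If they are imposed as fixed coefficients, no in-sample coefficient is estimated. But a general-population value (2.2-8.9 in the simulations) would be badly calibrated for a sample where the association is 0.24-1.15.

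**Section 4.5 speaks of all adults.** A reader might infer that fitting the unconditional model there is an equal cure. It is not: the adjusted odds ratio was 1.75 in all adults against 1.35 in UTI patients in the same run, and 1.45-2.09 against 1.25-1.64 in another set. Section 3.5 also lists no individual data for UTI-free adults.

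**Conclusion.** The point holds in limited form. On the extract and inclusion rule as written, history defined as any earlier UTI in 2014-2024 loses or reverses its association with UTI (about 0.24-1.15, against 2.2-8.9 in all adults, without event dependence). It therefore gives little or no control of stable UTI-proneness.

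The consequence for the primary odds ratio is conditional. If proneness and antibiotic use are positively correlated, the adjusted value is about 1.1-1.6 for non-UTI antibiotics with no true effect, and higher under a steeper link. If they are not correlated, there is essentially no inflation. With a 12-month look-back or event dependence the covariate works slightly to modestly and bias remains.

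The underlying fault is the pairing of a self-controlled label with a between-person model in a UTI-only sample. The history covariate is where that pairing most clearly fails.

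**What to change.** 1. In 3.1 and 6.2, replace the ordinary logistic model on the UTI-only extract with a person-conditional one (conditional Poisson self-controlled case series, or conditional logistic regression). Replace or condition the Cox model on the same principle.
2. Remove history of UTI and other time-fixed traits from its covariate list. Keep season and factors that change over time. Conditioning removes stable differences only, so time-varying confounding still needs these terms.
3. Make the non-UTI antibiotic analysis, already listed in 6.1, the one interpreted as free of this bias. Handle UTI-indicated antibiotics separately, because that exposure follows from an earlier event and biases the within-person estimate. The all-infections odds ratio in 6.1 inherits that problem and should not be read as if conditioning had cured it.
4. Reconcile 3.5, 4.5 and 5.1 on whether the analysis population is UTI patients or all adults.
5. Do not offer the unconditional all-adults model as an equivalent alternative.

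The cost is protocol wording and a different model call. No wider extract is needed, and 3.5 already asks for the diagnosis attached to each prescription, which allows the split by indication.
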